## Abstract

**Introduction:**

Autism spectrum disorders (ASDs) are associated with difficulties in social interaction, communication and restricted, repetitive behaviours. Much is known about their community prevalence among adults, data on adult inpatients within an acute mental health setting is lacking.

This pilot study aimed to estimate the prevalence of ASDs among adults admitted to acute mental health wards and to examine the association between ASDs and psychiatric and physical comorbidities within this group.

**Methods and analysis:**

A multiple-phase approach will be used. Phase I will involve testing of 200 patients and corresponding informants, using the autism quotient (AQ), the informant version of the Social Responsiveness Scale, second edition—Adult, the self and informant versions of the Adult Social Behaviour Questionnaire and the EuroQol-5D-5L. Patients with intellectual disability (ID) will bypass Phase I.

Phase II will involve diagnostic testing of a subgroup of 40 patients with the Diagnostic Interview for Social and Communication Disorders, the Autism Diagnostic Observation Schedule version 2 and the ASD interview within the Schedules for Clinical Assessment in Neuropsychiatry version 3. 25±5 patients will not have ID and be selected via stratified random sampling according to AQ score; 15±5 patients will have ID. Phase II patients will be interviewed with the Physical Health Conditions and Mental Illness Diagnoses and Treatment sections of the 2014 Adult Psychiatric Morbidity Survey.

Prevalence estimates will be based on the proportion of Phase II participants who satisfy the 10th revision of the International Statistical Classification of Diseases and Related Health Problems Diagnostic Criteria for Research (ICD-10-DCR) and the 5th edition of the Diagnostic and Statistical Manual of Mental Disorders (DSM-5) diagnostic criteria for ASD, adjusting for selection and non-response. Univariate analysis will be conducted for comorbidities to identify the level of their association with an ASD diagnosis.

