25 found that children with ASDs experienced significantly higher levels of psychopathology compared with those with ID, a group which in itself is associated with an elevated risk of psychiatric disorder.^26^

However, it is unclear how the burden of psychiatric comorbidity seen in children with ASDs transitions into adult life.^27^ It is essential to understand this natural course of ASDs and its comorbidities in order to develop appropriate services to meet the needs of this patient group.^28^ Additionally, some psychiatric disorders, such as schizophrenia, do not typically manifest until late adolescence onwards,^29^ so child comorbidity studies into such disorders would be of limited value.

A scoping review by Cashin *et al*
30 found a lack of research pertaining to the physical health of individuals with diagnosed ASDs, and that most studies were limited to retrospective analysis of healthcare records rather than involving any form of direct health assessment. Additionally, these studies were focused on individuals with previously recognised ASD diagnosed through routine clinical assessment, rather than having been identified through population-based epidemiological studies. Current evidence suggests that children with ASDs are at greater risk of a range of comorbid physical illness compared with their non-ASD peers, including obesity,^31–33^ epilepsy,^34 35^ asthma,^35^ sleep disorders^36^ and gastrointestinal disorders.^36^ This assertion is further supported in a recent systematic review by Muskens *et al*,^37^ who described medical disorders across a range of medical areas (including immunology, neurology and gastroenterology) as being widespread among children with ASD. However, despite the relative paucity of research in child populations, even less is known about the burden of physical comorbidity among adults with ASDs.^38^

The aims of this prospective pilot study are to estimate the prevalence of ASDs among adults based on acute mental health inpatient units, as well as to examine the association between ASDs and other psychiatric and physical comorbidities within this group.

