**Figure 1 F1:**
[figure not shown]
Flow chart summary of study design. ASDs, Autism spectrum disorders; AQ, autism quotient

In terms of the multiple-phase design for non-ID patients, transition to Phase II will be selected via stratified random sampling according to the patient’s scores on the Autism Quotient (AQ)^41^ questionnaire (table 1). This weighted approach enables generation of a prevalence estimate for the population as a whole (compared with if there were a single threshold AQ score for Phase II progression) and has been extensively validated, including in the 2014 APMS.^13^

**Table 1 T1:** The probability of selection for Phase II according to total scores in the AQ questionnaire. This probability framework has been validated in a previous study conducted on adult participants from a mixture of inpatient and community mental health settings.^39^ Participants scoring higher on these questionnaires will have a greater probability of selection

AQ score	Probability of selection
≤19	0.1
20–24	0.2
25–29	0.3
30–39	0.6
≥40	1.0

The rationale for a single-phase design in patients with ID is twofold. First, there is a lack of validated and relevant ASD questionnaires for this patient group.^42^ Second, the prevalence of ASD in this patient group is substantially higher in community studies,^12^ such that a single-phase design would be less resource-inefficient in identifying individuals meeting ASD diagnostic criteria within this group.

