### Study population

The total sample will comprise 200 patients between the ages of 18 and 65 years, with a history of having been a psychiatric inpatient on an adult acute mental health ward during the study time period (from 6 March 2019 to 31 December 2020). The inclusion and exclusion criteria are summarised in table 2. Out of these 200 patients undergoing Phase I testing, 40 will transition to Phase II of the study. The Phase II patient group will consist of 25±5 non-ID patients, and 15±5 patients with ID.

**Table 2 T2:** Inclusion and exclusion criteria. Additionally, participants lacking capacity will be withdrawn from the study if they become distressed by the assessment process and/or their guardians are not in agreement with them remaining in the study

Inclusion criteria	Exclusion criteria
Aged between 18 and 65 years.	<18 or >65 years of age.
Being or having been a psychiatric inpatient on an adult acute mental health ward during the study time period.	Having no history of being a psychiatric inpatient on an adult acute mental health ward during the study time period.
	Clinical diagnosis of dementia.
	Not understanding written and/or verbal English.

Study participants will be recruited from two inpatient units based in Leicestershire, UK. These units serve a population of approximately 1 million people living in both urban and rural areas within Leicester, Leicestershire and Rutland.^43^ Applications to extend the study to further sites are currently in progress.

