### Data analysis plan

The primary outcome parameter will be based on patients who transition to Phase II of the study. The ASD prevalence estimate will be calculated based on the proportion of Phase II participants who meet the ICD-10-DCR and DSM-5 diagnostic criteria for ASD on clinical assessment, with adjustment for selection and non-response, as well as the different study designs for the ID and non-ID patient subgroups.

For the feasibility study, the analyses will be descriptive. For continuous variables, values and SD will be reported; for categorical variables, percentages and SD will be reported. We will use multiple imputation to account for any missing data. For the full-powered study, the generalised linear model will be used to estimate the difference between groups, as well as corresponding OR, 95% CI and p values.

The analyses will be primarily conducted in SPSS (version 26), but for more advanced statistical analyses (such as use of the generalised linear model) and graphical representation, we will use R.

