### Sample size justification

The sample size was calculated with direct statistician support, as well as the use of a statistical textbook and related software.^51^ For a significance level of 0.05 and power of 85%, assuming estimates of 1% community ASD prevalence and 5% inpatient ASD prevalence,^15^ a sample size of 374 patients is required. Ideally, we would be subjecting a minimum of 374 patients to Phase II testing. This is because only participants completing Phase II interview assessments will yield data pertaining to the primary outcome variable (ie, the presence or absence of satisfying diagnostic criteria for ASD).

However, in the first instance, around 40 patients (from the minimum of 200 subjected to Phase I testing) will be selected for Phase II testing (via stratified random sampling for non-ID patients, whereas ID patients will progress automatically to Phase II). The Phase I sample size of 200 patients takes into account the probability sampling method for Phase II selection, in addition to allowing for losses to follow-up for Phase I participants invited for Phase II testing. Our results will assume that the data for these 40 patients are representative of the larger group subjected to Phase I testing. Owing to the sample size, the SPRINT study shou

ld be considered a pilot/feasibility study, the intention of which being to establish and further refine the technical, administrative and logistical aspects of the study, with a view towards sample size expansion on its completion. The sample size represents an appropriate sample size for a feasibility study of this type.^52 53^

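### The abstract promises univariate ASD–comorbidity associations from the pilot while the analysis plan allows only description; a crude comparison in the ID-enriched, AQ-sampled Phase II group could mislead in either direction

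*Protocol article*

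**What the plan says.** All references are to the protocol article.

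- **Abstract, Methods and analysis:** "Univariate analysis will be conducted for comorbidities to identify the level of their association with an ASD diagnosis". The preceding sentence, on prevalence, carries an adjustment for selection and non-response; this one carries none.
- **Abstract and Introduction (aims):** the pilot is meant "to examine the association between ASDs and other psychiatric and physical comorbidities within this group".
- **Data analysis plan:** "For the feasibility study, the analyses will be descriptive". Odds ratios, confidence intervals and p values are placed later: "For the full-powered study, the generalised linear model will be used to estimate the difference between groups". Adjustment for selection, non-response and the differing ID and non-ID designs is attached to the prevalence estimate.
- **Study population:** Phase II consists of "25±5 non-ID patients, and 15±5 patients with ID".
- **Table 1:** "Participants scoring higher on these questionnaires will have a greater probability of selection". The probabilities are 0.1, 0.2, 0.3, 0.6 and 1.0 for AQ ≤19, 20–24, 25–29, 30–39 and ≥40.
- **Sample size justification:** non-ID patients are sampled, "whereas ID patients will progress automatically to Phase II". Only patients who complete Phase II contribute an ASD diagnosis.
- **Strengths and limitations:** the design is said to allow ID and non-ID patients to be considered separately. This is not tied to the comorbidity analysis.

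**The concern.** Association with comorbidity is one of the study's two aims, and the article describes two different analyses for it. A reader of the abstract expects a measured association from this pilot. A reader of the analysis plan expects description now and comparison later.

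The method named in the abstract also fits the sample poorly. A univariate comparison does not adjust for ID. On the article's own evidence, ID is related to ASD: the Introduction cites 42.3% (men) and 35.2% (women) in moderate to profound ID, against 1.1% overall. The Introduction also says ID carries a raised risk of psychiatric disorder. A factor related to both sides of a comparison, and making up over a third of the sample, can produce or hide an association when the groups are combined. The non-ID patients are in addition an unequal-probability sample. If a crude odds ratio were published from these data, a reader could tell neither the size nor the sign of the distortion.

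**Working it through.** **The plan's own figures.** No figure is given for the comorbidity analysis. The one computed number, 374, concerns prevalence and does not enter here.

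**Step 1. Composition of Phase II.** ID share = 15/40 = 37.5%; with the ±5 tolerance and 40 in total, 10/40 = 25% to 20/40 = 50%. Among all recruits it is 15/200 = 7.5%, or 15/215 = 7.0% if the ID patients are additional to the 200. ID patients are therefore over-represented about five-fold.

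**Step 2. Effect of pooling ID and non-ID.** Take 15 ID and 25 non-ID patients. Let p be the ASD proportion and e the comorbidity proportion in each group, with comorbidity independent of ASD inside each group (true odds ratio 1.0). Expected cells, summed over the two groups:

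- a (ASD, comorbid) = Σ n·p·e
- b (ASD, not comorbid) = Σ n·p·(1−e)
- c (no ASD, comorbid) = Σ n·(1−p)·e
- d (no ASD, not comorbid) = Σ n·(1−p)·(1−e)
- pooled OR = ad/(bc)

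The group sizes come from the article. The 1% is its figure for mild ID, and 38% lies within its 35.2–42.3% for moderate to profound ID. The 20%, the non-ID ASD rates and all comorbidity rates are assumptions.

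| ASD in ID | ASD in non-ID | Comorbidity in ID | Comorbidity in non-ID | a, b, c, d | Pooled OR | ASD cases |
|---|---|---|---|---|---|---|
| 38% | 8% | 20% | 2% | 1.18, 6.52, 2.32, 29.98 | 2.34 | 7.7 |
| 38% | 8% | 20% | 5% | 1.24, 6.46, 3.01, 29.29 | 1.87 | 7.7 |
| 20% | 8% | 20% | 5% | 0.70, 4.30, 3.55, 31.45 | 1.44 | 5.0 |
| 38% | 5% | 25% | 3% | 1.46, 5.49, 3.04, 30.01 | 2.63 | 7.0 |
| 1% | 8% | 20% | 5% | 0.13, 2.02, 4.12, 33.73 | 0.53 | 2.2 |

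A wider grid used the article's 35.2–42.3% in ID and an assumed 5–20% in selected non-ID patients:

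- Comorbidity 20% in ID and 5% in non-ID: OR 1.32–2.15.
- Comorbidity 30% in ID and 60% in non-ID: OR 0.50–0.80.
- With 1% ASD in ID instead, these become 0.45–0.59 and 1.40–1.62.
- Comorbidity equally common in both groups: OR exactly 1.00.

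Stratifying by ID returns 1.0 throughout, by construction.

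**Step 3. Effect of AQ sampling alone (non-ID).** Let s be the mean Table 1 selection probability in each ASD-by-comorbidity group, with the first index for ASD and the second for comorbidity. With a true OR of 1, the unweighted OR is s11·s00/(s10·s01). AQ is assumed normal with SD 7, mean 18–24 without ASD and 30–35 with ASD.

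- Comorbidity does not shift AQ: OR = 1.00.
- Mildest case (means 24 and 30, shift of 3 points): 0.564 × 0.291/(0.465 × 0.373) = 0.95.
- Strongest case (means 18 and 35, shift of 8 points): 0.868 × 0.175/(0.631 × 0.344) = 0.70.

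Weighting by the inverse of the Table 1 probabilities returns 1.0.

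**Step 4. Precision.** With k ASD cases among 40 and a 50% comorbidity, SE(log OR) = √(4/k + 4/(40−k)). The 95% interval around OR = 1 is exp(±1.96·SE):

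- k = 5: SE 0.956, interval 0.15–6.5
- k = 8: SE 0.791, interval 0.21–4.7
- k = 10: SE 0.730, interval 0.24–4.2

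**The case against.** A reader might infer that the plan will pool ID and non-ID patients, ignore the sampling weights and so manufacture positive associations. The documents do not support that, for four reasons.

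- No section says the comorbidity comparison will be pooled or unweighted. A univariate comparison can be made within ID groups and with weights. The strengths list mentions separate consideration, and the Data analysis plan shows that the authors know selection and the two designs need adjustment. Further detail may sit in a fuller document.
- The distortion is conditional. It needs comorbidity to differ by ID status or to shift AQ, and the article gives no comorbidity rates by ID.
- The direction is not fixed. Odds ratios above 1 in Step 2 follow from choosing high ASD prevalence and high comorbidity in ID. The severity mix of the ID inpatients is not stated, and the mild-ID figure reverses the sign.
- AQ sampling left the odds ratio at 1.00 or moved it below 1. It did not produce positive associations.

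It can also be said that a cross-tabulation is both univariate and descriptive, and that the abstract promises no p values. That softens the conflict without removing it: the abstract's stated purpose is to identify a level of association, and the Data analysis plan names no association analysis for the pilot.

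What survives is the mismatch between sections, together with the fact that the only method named for this aim leaves unadjusted a factor that the article itself links to ASD and to psychiatric disorder.

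**Conclusion.** The point holds in a limited form. The abstract and aims promise an association analysis from this pilot; the Data analysis plan restricts the pilot to description and defers comparison. That conflict is in the text and needs no assumption.

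The statistical consequence is a possibility. If ID and non-ID patients are compared as one group, a null association could appear as an odds ratio of about 1.4–2.6, or as about 0.5, depending mainly on how common ASD is among the ID patients recruited. If AQ weights are left out, the effect is nil unless the comorbidity shifts AQ, and about 0.70–0.95 if it does. These sizes rest on assumed comorbidity rates, non-ID ASD rates and AQ distributions. With 5 to 10 ASD cases, even an unbiased pilot odds ratio would be too imprecise to interpret. The primary prevalence outcome is not affected.

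**What to change.** 1. Align the abstract with the Data analysis plan. Keep the aim, but say that in the pilot comorbidity will be described by ASD status.
2. Present those tables separately for ID and non-ID patients. In the non-ID group weight by the inverse of the Phase II selection probability (from 1/1.0 = 1 to 1/0.1 = 10 under Table 1), and show unweighted counts alongside. Give no p values.
3. For the full-powered study, state that where "the generalised linear model will be used to estimate the difference between groups", the model will include ID status and the selection weights.

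The cost is a few sentences, and the Table 1 probabilities are already fixed by design. The downside is that the pilot gives no pooled odds ratio or p value and the stratum tables will be sparse: at 5–8% ASD, 25 non-ID patients yield 25 × 0.05 = 1.25 to 25 × 0.08 = 2 expected cases. Weighted percentages on so few cases will be unstable and should be labelled as such.

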**Ethics and dissemination:**

Study oversight is provided by the University of Leicester. The National Health Service Health Research Authority have provided written approval. Study results will be disseminated via conference presentations and peer-reviewed publications.

**Trial registration number:**

ISRCTN27739943

Strengths and limitations of this studyThe study is currently limited to a single site, limiting its generalisability. However, applications to extend to other sites are currently in progress.The planned sample size is in keeping with a pilot study, although there are plans to expand to a larger trial on completion.The primary outcome measure (meeting the diagnostic criteria for autism spectrum disorders (ASDs)) is somewhat contingent on the diagnostic criteria used, although internationally recognised criteria have been used (the ICD-10-DCR and DSM-5).The study will be conducted under double-blind conditions, whereby neither patients nor health professionals conducting Phase II clinical assessments will have knowledge of the participants’ corresponding Phase I questionnaire results.The study design allows consideration of patients with and without intellectual disabilities separately, in contrast to many other studies of its type.

## Introduction

Autism spectrum disorders (ASDs) are lifelong neurodevelopmental conditions characterised by impairments in reciprocal social interaction and communication, as well as restricted, stereotyped and repetitive behaviours.^1^ These difficulties should manifest prior to 3 years of age, thus a detailed developmental history forms a key part of the diagnostic assessment process. Although originating in childhood, ASDs follow a persistent course throughout adult life.^2^ While the level of impairment associated with ASDs varies between individuals, the impact on both those with ASD and their families is always profound.^3^

The diagnostic criteria for ASD according to the ICD-10-DCR^4^ and DSM-5^5^ diagnostic classification systems are summarised in box 1. It should be noted that the transition from DSM-IV to DSM-5 criteria for ASD appears to reduce the number of individuals satisfying the diagnostic criteria, with only about 50%–75% of individuals maintaining diagnoses, a phenomenon which disproportionately affects higher functioning non-intellectually disabled (non-ID) individuals.^6^ However, the vast majority of what is known about ASD comes from research involving child populations, with less than 15% of UK-based ASD research being focused exclusively on adults,^7^ with a similar focus on children seen internationally.^8^

Box 1Summaries of the ICD-10-DCR4 and DSM-55 diagnostic criteria for ASD. For the diagnostic criteria in full, please refer to the source texts.ICD-10-DCR Criteria for Childhood Autism*Presence of abnormal or impaired development before the age of three yearsQualitative abnormalities in reciprocal social interactionQualitative abnormalities in communicationRestricted, repetitive and stereotyped patterns of behaviour, interests and activitiesThe clinical picture is not attributable to the other varieties of pervasive developmental disorder; specific developmental disorder of receptive language with secondary socioemotional problems; reactive attachment disorder or disinhibited attachment disorder; mental retardation with some associated emotional or behavioural disorder; schizophrenia of unusually early onset; and Rett’s syndrome.DSM-5 Criteria for Autism Spectrum DisorderPersistent deficits in social communication and social interaction across multiple contextsRestricted, repetitive patterns of behaviour, interests or activitiesSymptoms must be present in the early developmental periodSymptoms cause clinically significant impairment in social, occupational or other important areas of current functioningThese disturbances are not better explained by intellectual disability (ID)†*ICD-10-DCR also recognises the diagnosis of ‘atypical autism’, whereby the features of abnormal development only manifest for the first time after 3 years of age (A) and/or the affected individual does not satisfy all three of the clinical diagnostic criteria (B-D).†DSM-5 recognises that ASD and ID frequently coexist, but that “to make comorbid diagnoses of autism spectrum disorder and intellectual disability, social communication should be below that expected for general developmental level.”

When autism was first described in the medical literature, it was considered a rare condition.^9^ However, there has been a significant rise in reported prevalence estimates in recent decades, which has been attributed to a myriad of factors, including broadening of diagnostic criteria, changes in study methodology, increasing knowledge of ASD among lay persons and professionals, and possibly a genuine increase in prevalence.^10^

ASDs represent a major global public health issue, responsible for over 111 disability adjusted life years per 100 000 persons.^11^ Community-based prevalence rates for ASDs in adults within the general population show considerable variation across studies over time, although a recent large-scale epidemiological study estimated a prevalence rate of 1.1% (95% CI 0.3 to 1.9).^11 12^

A large UK-based study of 7274 participants in the 2014 Adult Psychiatric Morbidity Survey (APMS)^13^ coupled with a register of 290 adults with intellectual disability (ID), defined by DSM-5 as deficits in intellectual functioning (typified by an IQ score of ≤70) coupled with deficits or impairments of adaptive functioning, with onset during the developmental period found an overall estimated ASD prevalence of 1.1% (95% CI 0.3% to 1.9%).^12^ This is in keeping with the findings of a child study of 56 946 participants by Baird *et al*,
14 who found an overall estimated prevalence of ASDs of 116.1 per 10 000 (95% CI 90.4 to 141.8). However, while the Brugha *et al*
12 ASD prevalence findings for people with mild ID (1.0%, 95% CI 0.4 to 2.2) were similar to the overall findings, those with moderate to profound ID had a markedly increased risk of ASD, with prevalence rates of 42.3% (95% CI 31.1 to 54.3) and 35.2% (95% CI 23.5 to 49.0) in male and female, respectively.

However, relative to the community setting, there has been very little research into the prevalence of ASDs among adults within acute mental health inpatient settings.^15^ Previous work appears to suggest that the prevalence of ASDs could be significantly greater in this group than that of the general population and that they may be substantially underdiagnosed in this group, with prevalence estimates varying from 1.5% to 9.9%.^16–19^

The vast majority of research on psychiatric comorbidity in patients with ASDs has been conducted in child and adolescent populations.^20^ Such studies have shown high rates of comorbid psychiatric conditions among individuals with ASDs, with rates ranging from 70.8%^21^ to 80.9%,^22^ and commonly comorbid conditions including anxiety disorders, obsessive compulsive disorders, phobias, oppositional defiant disorder and attention deficit hyperactivity disorder.^21–25^ Notably, a study by Brereton *et al*
25 found that children with ASDs experienced significantly higher levels of psychopathology compared with those with ID, a group which in itself is associated with an elevated risk of psychiatric disorder.^26^

However, it is unclear how the burden of psychiatric comorbidity seen in children with ASDs transitions into adult life.^27^ It is essential to understand this natural course of ASDs and its comorbidities in order to develop appropriate services to meet the needs of this patient group.^28^ Additionally, some psychiatric disorders, such as schizophrenia, do not typically manifest until late adolescence onwards,^29^ so child comorbidity studies into such disorders would be of limited value.

A scoping review by Cashin *et al*
30 found a lack of research pertaining to the physical health of individuals with diagnosed ASDs, and that most studies were limited to retrospective analysis of healthcare records rather than involving any form of direct health assessment. Additionally, these studies were focused on individuals with previously recognised ASD diagnosed through routine clinical assessment, rather than having been identified through population-based epidemiological studies. Current evidence suggests that children with ASDs are at greater risk of a range of comorbid physical illness compared with their non-ASD peers, including obesity,^31–33^ epilepsy,^34 35^ asthma,^35^ sleep disorders^36^ and gastrointestinal disorders.^36^ This assertion is further supported in a recent systematic review by Muskens *et al*,^37^ who described medical disorders across a range of medical areas (including immunology, neurology and gastroenterology) as being widespread among children with ASD. However, despite the relative paucity of research in child populations, even less is known about the burden of physical comorbidity among adults with ASDs.^38^

The aims of this prospective pilot study are to estimate the prevalence of ASDs among adults based on acute mental health inpatient units, as well as to examine the association between ASDs and other psychiatric and physical comorbidities within this group.

